### Sample size estimation

Pilot RCT guidance suggests that where sample size is calculated, it be based on the ability to detect a significant feasibility problem that might interfere with a subsequent full-size RCT—for example, difficulty with recruitment and retention, accuracy of outcome event capture and adjudication, frequency of events, and costing suggesting the intervention is not remotely cost-effective [55]. If a feasibility problem exists at a rate of 5% probability, it can be identified with 95% confidence with a sample of 59 participants [55].

### Recruitment methods

Background work flow studies at several of the participating hospitals have confirmed that patient discharge is a complex, hurried process that is often rescheduled multiple times because of fluctuations in patient health or delays in required tests, procedures, or milestones. For feasibility reasons, we plan to use a rolling recruitment method, spending 2 weeks at each hospital on a cyclical basis until a quota is recruited (10–12 patients per site). Rounds and recruitment posters will advertise the study; in some locations, the EMR can assist with screening criteria, and in all locations, research staff are seeking eligible patients in consultation with the Most Responsible Physician team personnel.

### Allocation

Participants who meet all the inclusion/exclusion criteria at screening and have completed informed consent will be enrolled in the study, complete baseline assessments, then will be randomized via a computer-generated randomization sequence stratified by site to one of the two study arms, intervention, or control.

A statistician will prepare the randomization schedule using an adaptive biased-coin strategy [56]. Randomization will be stratified by site to maintain balance and minimize the predictability of treatment assignments [57]. To restrict the treatment group imbalance, a maximal tolerable imbalance between treatment groups will be incorporated into the schedule [58]. The randomization schedule will be produced by a program written in SAS V9.4 software (SAS Institute Inc., Cary, NC, USA) and implemented in REDCap on a centralized computer where each patient’s treatment assignment will be available on-line to the research pharmacist at the time of randomization. This process ensures allocation concealment, and randomization awareness where necessary, for example, for the intervention staff.

### Blinding

Since this is a pragmatic RCT of care coordination, it will not be possible to completely blind patients or their providers; however, outcome data collectors, adjudicators, and statisticians will be blinded to group allocation until analysis is completed at the end of the study.

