### Outcomes

Study outcomes, their measurement methods, timing, and analysis are presented in detail in Table 1 and Table 2 and include the following:Primary outcomes, which are study feasibility outcomes, include recruitment and retention rates, and estimated resources required per patient to complete the main trial. Feasibility will be achieved if we can recruit at least 30% of those eligible, retain 90% of those recruited, and spend no more than $1500 per patient running the trial. Secondary feasibility outcomes include barriers and facilitators to success of the primary outcomes, in terms of process and management issues. These will be used to determine whether a large definitive research study is likely to be feasible, taking into account the practical aspects of managing and funding the project [41, 42].Secondary clinical outcomes include the following:The Adverse Anticoagulant Safety Events composite (AASE) which is any of thromboembolic events or clinically relevant bleeding or death. Thromboembolic events include objectively verified ischemic stroke, systemic embolism, pulmonary embolism, or DVT. Clinically relevant bleeds in this study is defined as bleeding that causes death, hospitalization, or emergency department visits.Coordination and Continuity of Care: Adapted from Health Quality Ontario’s draft guidance and a Rand instrument, the Coordination and Continuity of Care Questionnaire is designed to measure the quality of the transitional and follow-up care [5, 43, 44].Patient Quality of Life: The EQ-5D-5L is the 5-level classification system of the EQ-5D, a measure of health status from the EuroQol group [45]. Using EQ-5D-5L, respondents are asked a short series of questions about mobility, self-care, usual activities, pain discomfort, and anxiety/depression, as well as a summary visual analogue scale. This scale, which provides utility measurements, has been well validated for the Canadian population [45–47].Patient Knowledge of OAC Management: Insufficient patient knowledge about OAC may predict poor medication adherence and inadequate anticoagulation control [48]. The COACHeD OAC Knowledge Questionnaire tests knowledge of the therapeutic objective, process of use, safety, and maintenance of the medications [44].Satisfaction with Care: Satisfaction reported by patients and by key health professionals is one of the recommended outcomes to report in medical research, as it may influence adherence [49, 50]. This outcome will be assessed by the Patient/Caregiver Study Satisfaction Survey and by the Provider Study Satisfaction Survey [44].Medication Problems: We will be assessing problems with appropriateness, with medication errors characterized using the National Coordinating Council for Medication Error Reporting and Prevention (NCC-MERP) scale and with medication adherence and attitudes as measured by COMPETE Medication Problems Questionnaire [51, 52].Resource utilization: This is a key outcome to determine cost-effectiveness and cost-utility which then determines whether health care systems might pay for this type of care [53, 54]. We will be measuring all types of health care utilization by patients [43, 46, 54].

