**A. Feasibility outcomes**					
Primary feasibility outcomes	Participant recruitment rates	Continuous (%)	≥ 30% of those eligible will be considered success	Percentage recruited and rate of recruitment (of those screened, of those eligible, and of those approached). Percentage of those recruited (signed informed consent) who complete the end of study assessment at 3 months.	Count of percentages and rates over time
	Participant retention rate	Continuous (%)	≥ 90% is considered success		
	Study resource utilization	Continuous ($CND)	< $1500 per patient recruited and completing the study	Study costs per patient recruited	Cost of personnel, supplies, travel, etc., to run the study/# patients recruited
Secondary feasibility outcomes	Process assessments Management assessments Scientific assessments	Mix of continuous, categorical, and qualitative data	Implementation is successful and feasible, questionnaires are acceptable, and data gathered are reliable and valid	Detailed questions in feasibility assessment	Descriptive
**B. Clinical outcomes**	**Hypothesis**				
Primary clinical outcome	Adverse anticoagulant safety event composite (AASE)	Continuous (%)	Intervention group will have fewer AASE compared to the control group	Count of AASE at the end of the study (3 months). Rates will be expressed as mean rate per patient-year by research assistant.	Chi-square test
Secondary clinical outcomes	Coordination and continuity of care	Continuous	Intervention will have higher ratings than control	Coordination and continuity of care questionnaire partially administered post-discharge and finalized at study end (3 months) by telephone.	*T* tests
	Patient quality of life	Continuous	Intervention will improve more than control	EQ5D-5L—difference in mean change scores at the end of the study.	*T* tests
	OAC management knowledge - patient	Continuous	Intervention will have higher scores than control	OAC knowledge questionnaire	*T* tests
	Satisfaction with care (providers & patients)	Continuous	Intervention will have higher scores than control	Satisfaction questionnaires	Descriptive analysis
	Medication Problems	Continuous	Intervention will have fewer medication problems than control	Composite of OAC-APEQ, COMPETE adherence, and medication error scores	*T* tests
	Cost-effectiveness	Continuous	Intervention will be cost-effective compared to control using a threshold of $50,000 per QALY.	Cost per AASE avoided and cost per quality-adjusted life-years (QALYs)	Economic analysis

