	Individual Clinical Events: a) Bleeding events (clinically relevant), b) Thromboembolic events (all); c) Deaths; d) Hospitalizations or ED visits	Continuous	Intervention will have lower event rates than control	Event rate counts from end-study interviews	*T* tests

**Table 2 Tab2:** COACHeD schedule of events

Assessment	Enrolment		Study in-progress			Study end
	Baseline	Hospital discharge	24h	1Week	1 month	3 months
Eligibility screen	A					
COACHeD Brief Assessment of Capacity to Consent	B					
Informed consent	1/C					
Coordination Continuity of Care Questionnaire (CCCQ)	I/C					I/C
EQ-5D-5L v10-Canada	1/C					I/C
OAC knowledge test	I/C					I/C
Randomization and allocation	I/C					
Discharge medication reconciliation and management, circle of care communication and coordination		I				
Virtual Visit Call #1			I			
Virtual Visit Call #2				I		
Virtual Visit Call #3					I	
Adverse anticoagulant safety events (AASE)						I/C
AASE individual components						I/C
Patient/Caregiver Satisfaction Questionnaire						I/C
Provider Satisfaction Questionnaire						I/C
Health Resource Utilization Questionnaire						I/C
Medication-related problems						I/C

*A*, all potentially eligible patients; *B*, all eligible and interested patients; *I*, intervention patient; *C*, control patient; *I/C*, both groups

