### Data collection methods

Trained research staff will conduct the interviews with the patients or caregivers, entering data electronically on study laptops directly into REDCap case report forms. The participants’ medical records will be reviewed to abstract data on baseline characteristics, medical history, and medication information. Strategies to promote participant retention and complete follow-up include reminding participants in advance of their end-of-study visit and communicating by email if email address is provided at baseline. Participants who drop out of the study will have their data to that point retained in the study, as approved by REB, to avoid bias. The reasons for study non-completion will be recorded.

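### Outcome collectors are said to stay blinded until analysis is complete, but the 3-month instruments make that hard to keep, and no safeguard is stated for AASE collection

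*Protocol article*

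**What the plan says.** The Blinding section concedes that "it will not be possible to completely blind patients or their providers" and then states, without qualification, that "outcome data collectors, adjudicators, and statisticians will be blinded to group allocation until analysis is completed at the end of the study". Trial design and setting likewise describes the assessment as blinded.

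Table 2 gives the 3-month time point, in both arms, to AASE, its components, health resource use, the coordination and continuity questionnaire, EQ-5D-5L, the knowledge test and the "Patient/Caregiver Satisfaction Questionnaire". The Outcomes section calls the satisfaction instruments the "Patient/Caregiver Study Satisfaction Survey and by the Provider Study Satisfaction Survey", and says that the continuity questionnaire rates care during and after the transition home. Table 1 has that questionnaire completed by telephone at 3 months.

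For the individual clinical events, Table 1 gives the source as "Event rate counts from end-study interviews". Data collection methods says: "Trained research staff will conduct the interviews with the patients or caregivers, entering data electronically on study laptops directly into REDCap case report forms". Statistical analyses makes adjudicated AASE the primary clinical endpoint, below feasibility in this pilot.

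**The concern.** The blinding claim covers every outcome data collector up to the end of analysis. Continuity of care and satisfaction are listed outcomes, so whoever collects them falls under it. These instruments ask about what differs between the arms. One arm had pharmacologist-led discharge management and three pharmacist visits; the other had usual care and a website address. A patient who answers candidly will often disclose which.

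The consequence of interest is for AASE. If the person eliciting events already knows the arm, questions may be pressed harder in one arm than in the other. Blinded adjudicators can classify only what reaches them and cannot recover an event that was never reported. Sample size estimation itself names accuracy of event capture and adjudication among the problems that a pilot should detect, so a weakness here bears on what this trial is meant to learn.

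**Working it through.** **The plan's own figure.** The article's only sample-size figure reproduces: n = ln(1 − 0.95)/ln(1 − 0.05) = 58.40, rounded up to 59. The chance of seeing at least one problem is 0.9515 with 59 participants and 0.9490 with 58. Nothing here disputes it. It gives 59/2 = 29.5, or about 30 per arm. The site quotas (6 sites × 10 to 12 = 60 to 72) give 30 to 36 per arm.

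**The sections side by side.**

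1. Blinding: collectors are blinded until analysis is complete; patients are not fully blinded.
2. Outcomes and Table 1: the continuity questionnaire concerns the care that the intervention changes, and it is finished by telephone, so a member of staff hears the answers. This already strains the claim for that collector, whoever collects AASE.
3. Table 2: AASE and its components share that time point.
4. Table 1 and Data collection methods: individual event counts come from interviews held by research staff. The record review described there covers baseline characteristics, history and medications; outcome events are not named.
5. Nowhere in the article: an order of instruments, a lock on the AASE form, separate staff for the care questionnaires, or a record of whether blinding held.

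Items 1 and 2 show that the general claim is too broad. Items 3 to 5 show that AASE collection is exposed. They do not show that it was compromised.

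**What one event is worth.** 1/30 = 3.3 percentage points of an arm's risk (1/36 = 2.8 at the larger quota). This follows from arm size alone and is not evidence of bias.

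**Illustration on assumed values.** The article gives no AASE rate and no ascertainment figures. Assume no true effect, the same true risk p in both arms, and 30 patients per arm, with one arm's events elicited at a fraction s of the other's. Then the spurious risk difference is p(1 − s), the apparent risk ratio is s, and the expected number of missed events is 30p(1 − s).

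| p | s | Spurious difference (points) | Events missed per 30 |
|---|---|---|---|
| 5% | 0.95 | 0.25 | 0.08 |
| 5% | 0.80 | 1.0 | 0.30 |
| 10% | 0.95 | 0.5 | 0.15 |
| 10% | 0.80 | 2.0 | 0.60 |
| 20% | 0.95 | 1.0 | 0.30 |
| 20% | 0.80 | 4.0 | 1.20 |

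The range is 0.25 to 4.0 points, or about 0.1 to 1.2 events. It shows scale only; the document supports no particular row.

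**The case against.** A fair defence has four parts.

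- **The central link is inferred.** No section says that one person, or one call, covers the care questionnaires and the AASE questions, and the mode of the satisfaction survey is not given. Form order and staffing are details that a journal article may leave to a manual. This stands. A reader might infer a flat contradiction, with the same collector giving everything together, and the article does not support that. What remains is a property that the article asserts for all collectors and that its own schedule makes hard to keep.
- **Table 2 is not an interview script.** A reader might take its row order to mean that continuity is asked before AASE. The rows follow first occurrence: the continuity questionnaire sits higher because it is also a baseline instrument. Read as a script, the table would put AASE before satisfaction. This stands, and the point does not rest on row order.
- **AASE is fairly hard.** Its components are death, objectively verified thromboembolism, and bleeding leading to death, hospitalization or an emergency visit, and adjudicators are blinded. Serious adverse events also go to the steering committee within a week of detection, so the interview need not be the only route. This stands and limits the risk to what is elicited and put forward.
- **Question order cannot guarantee a blind.** A patient may mention pharmacist calls while answering the AASE questions, and patients' own reporting is unblinded in any case. Table 1 also has part of the continuity questionnaire given after discharge, where Table 2 shows baseline and 3 months; a collector who made such a contact could already know the arm. This stands, and those two entries need reconciling.

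**Conclusion.** The point holds in limited form. The statement that all outcome collectors remain blinded until analysis is complete is broader than the design secures. The continuity and satisfaction instruments are likely to reveal the arm to whoever collects them, and AASE is gathered at the same time point with no stated safeguard.

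This rests on one judgement, that answers about follow-up care will often disclose the arm, and on no assumption about who makes the call. The effect on AASE cannot be quantified from the document. Under the assumed values it is small in absolute terms, although one event is 3.3 points in an arm of 30.

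A reader might conclude that the AASE comparison is biased, or that asking AASE first would fully protect it. The documents support neither. No recruitment, retention or cost criterion is affected. The change is still worth making, because it is nearly free and improves ascertainment of the main clinical outcome.

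**What to change.** At the 3-month contact:

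1. Open with a scripted request that the patient or caregiver not describe the care received until asked.
2. Elicit AASE and its components first, and lock those REDCap forms before the resource use, continuity and satisfaction forms open.
3. Add a field in which the collector records whether the arm became known and at which form.
4. Restate Trial design and setting and Blinding: claim blinding for adjudication and analysis; describe it as attempted, with unblinding recorded, for AASE collection; make no such claim for the continuity and satisfaction instruments.

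This reduces the risk and does not remove it. The cost is a form-order setting, a short script, one extra field and a slightly weaker blinding claim. The sample size, the chi-square test and the outcome definitions are unchanged. The recorded unblinding also gives the full-size trial direct information on how well blinded collection can be kept.

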### Data collection methods

Trained research staff will conduct the interviews with the patients or caregivers, entering data electronically on study laptops directly into REDCap case report forms. The participants’ medical records will be reviewed to abstract data on baseline characteristics, medical history, and medication information. Strategies to promote participant retention and complete follow-up include reminding participants in advance of their end-of-study visit and communicating by email if email address is provided at baseline. Participants who drop out of the study will have their data to that point retained in the study, as approved by REB, to avoid bias. The reasons for study non-completion will be recorded.

### Data management

REDCap (Research Electronic Data Capture) is our study software platform—secure, web-based, providing interfaces for validated data capture, role-specific access, audit trails for tracking data manipulation and exports, automated export procedures to SAS and encrypted transmissions [59, 60]. Paper study documents including signed informed consent forms will be stored in our secure research office once they are scanned into REDCap study files. Regular data quality checks, such as automatic range checks, will be performed by the study team to identify data that appear inconsistent, incomplete, or inaccurate.

Patients are not identifiable in the project results database. The identifying information required for the clinical team to deliver the intervention is kept in a separate database. Access to the final dataset will be restricted to the core research team.

### Statistical analyses

The reporting of the results of this trial will follow the CONSORT extension to pilot trials [41]. We will use descriptive statistics for presentation of baseline variables and adequacy of follow-up. Feasibility analysis including recruitment rate (≥30% is considered success), participant retention rate (≥90% to end of study is considered success), study resource utilization required (CAD $1500 per patient recruited and completing the study is considered a threshold), management assessment, and scientific assessment will be descriptive.

Analysis will use intention-to-treat methods with censoring only if the patient dies or drops out of the study with refusal of negotiated further assessments. A sensitivity analysis of the subgroup of patients who received all 3 planned follow-up intervention calls and completed the end-study data collection (per protocol analysis) will be carried out. Research staff and statisticians will review outcome data and analysis blinded to group identification.

The primary clinical endpoint will be the incidence of adjudicated AASE during the follow-up period, using proportions, and chi-square testing. Secondary endpoint analyses of the coordination and continuity of care, patient quality of life, OAC management knowledge satisfaction with care (providers & patients), and resource utilization will be analyzed using *t* tests. The incidence of the adjudicated individual clinical events (clinically relevant bleeding events, thromboembolic events, all-cause hospitalizations, and emergency department visits) will be analyzed using the methods described above for AASE. Public unit costs from Ontario will be used to cost healthcare resource utilization collected as part of the trial. Using an area under the curve approach, quality-adjusted life years (QALYs) will be determined by weighting the EQ-5D-5L health utility scores by time spent in health state. Costs and outcomes (i.e., QALYs, AASE) between the interventions will be compared from a public payer perspective. Given the short follow-up, a low risk of the trial and pilot design, no interim analysis or imputation for missing data is planned. All analyses will be performed using SAS V9.4 software (SAS Institute Inc., Cary, NC, USA).

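### The censoring rule treats death as a reason to censor although death is a component of AASE, and the text and Table 1 give conflicting analyses for the event outcomes

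*Protocol article*

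**What the plan says.** **Endpoint.** The Outcomes section of the protocol article describes AASE as a composite "which is any of thromboembolic events or clinically relevant bleeding or death". The Objectives section also names deaths among the adverse events of interest. Table 1 and the Statistical analyses section call AASE the primary clinical outcome or endpoint. The Outcomes section places it among the secondary outcomes, because the trial's primary outcomes are feasibility measures.

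**Censoring.** The rule in Statistical analyses is "Analysis will use intention-to-treat methods with censoring only if the patient dies or drops out of the study", where dropping out is limited to patients who also refuse later assessments. It stands as a general statement, and nothing restricts it to particular outcomes.

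**AASE analysis.** The text analyses adjudicated AASE "using proportions, and chi-square testing". The AASE row of Table 1 asks for a count at 3 months and adds "Rates will be expressed as mean rate per patient-year by research assistant", while still naming a chi-square test.

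**Individual events.** The text says that the adjudicated individual events "will be analyzed using the methods described above for AASE". Its list covers bleeding, thromboembolism, hospitalizations and emergency visits, but not deaths. The matching row of Table 1 does list deaths. It types the outcomes as continuous, gives the source as "Event rate counts from end-study interviews", and names t tests.

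**The concern.** An event that belongs to an endpoint cannot also be a reason to stop observing a patient for that endpoint. The censoring sentence puts death in the same class as refusal of further assessment. An analyst who applies it literally to AASE could treat a patient who dies without an earlier bleed or thromboembolism as incomplete rather than as having had an event. Deaths are the most serious component, and in a trial of about 60 patients a few of them can settle the observed AASE proportion. The AASE count also enters the planned cost per AASE avoided.

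The second problem is independent of the first. A proportion and a patient-year rate are different quantities, and a chi-square test on proportions addresses only the first. Individual events cannot be both adjudicated and tested like AASE, as the text says, and continuous interview counts compared by t tests, as Table 1 says. These are statements that conflict with each other, not detail left to an analysis plan.

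**Working it through.** **The article's own figure.** The only calculated number is the sample size of 59. It reproduces: ln(1 - 0.95) / ln(1 - 0.05) = 58.40, rounded up to 59. It rests on detecting a feasibility problem, not on AASE, so this point does not depend on it. The recruitment quota of 10-12 patients at each of 6 sites gives 60-72 patients; 60 is used below.

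**The passages side by side.**

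| Item | Statistical analyses (text) | Outcomes / Table 1 |
|---|---|---|
| Role of death in AASE | reason for censoring | component event |
| AASE measure | proportion | count, as a rate per patient-year |
| AASE test | chi-square | chi-square |
| Individual events, test | as for AASE (chi-square) | t tests, typed continuous |
| Individual events, source | adjudicated | end-study interviews |
| Deaths as an individual event | not listed | listed |

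The named test does not settle the first row. A chi-square on proportions has no place for censored follow-up, so a censored patient must be called an event, a non-event or outside the denominator. The article does not say which.

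**Size if deaths were censored and not counted.** The article gives no rates, so these are assumptions: 3-month non-fatal event risk p of 6-10% and death risk d of 3-5%, taken as independent. When a patient has both, the non-fatal event is taken to come first half the time.

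- AASE with deaths counted: A = 1 - (1 - p)(1 - d)
- Non-fatal event seen before death: B = p(1 - d/2)
- Share of first events lost: (A - B) / A

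| p | d | A | B | Share lost |
|---|---|---|---|---|
| 10% | 3% | 0.1270 | 0.0985 | 22% |
| 6% | 3% | 0.0882 | 0.0591 | 33% |
| 10% | 5% | 0.1450 | 0.0975 | 33% |
| 6% | 5% | 0.1070 | 0.0585 | 45% |

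The corners of the assumed ranges give 22-45%. In 60 patients the loss is 60 × 0.0285 = 1.7 patients at the low end and 60 × 0.0485 = 2.9 at the high end.

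A wider check assumes p of 5-10% and d of 2-10% and counts every non-fatal event, so that the share lost is 1 - p/A. It gives 15% (p = 10%, d = 2%: 1 - 0.10/0.118) to 66% (p = 5%, d = 10%: 1 - 0.05/0.145).

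**Chi-square against t test.** With events coded yes/no and 30 patients per arm:

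| Events per arm | Chi-square p (no continuity correction) | t test p |
|---|---|---|
| 1 v 6 | 0.044 | 0.045 |
| 2 v 6 | 0.129 | 0.133 |

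On binary data the choice barely matters. It matters more if Table 1 is followed literally, with counts or rates.

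**The case against.** The strongest reply is that the AASE definition governs. Death is an event by definition, and a proportion of patients with AASE can count it. Nowhere does the article call deaths non-events or remove them from the denominator. The censoring sentence may mean only that follow-up time ends at death, which suits a patient-year rate and outcomes that death cuts short, such as EQ-5D-5L. This stands as far as it goes: a reader might infer that following the plan drops deaths from AASE, and the documents do not support that. It does not remove the contradiction, because the sentence makes no exception and the text's list of individual events omits deaths as well.

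Three further inferences also go too far:

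- **That an effect on mortality would be hidden.** Table 1 lists deaths as an outcome of its own.
- **That deaths cannot be captured because the dead cannot be interviewed.** Data collection methods allows caregiver interviews, and Data monitoring has serious adverse events reviewed within a week of detection.
- **That the pilot AASE risk will set the size of the full trial.** The article does not say so. The sample size section names event frequency only as an example of something a pilot may examine.

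It is also fair to say that the conflict over tests is numerically small on yes/no data, that it does not cause any loss of deaths, and that hospitalizations and emergency visits can recur, so a count is not absurd for that row.

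**Conclusion.** The point holds as a contradiction in the stated text. One general rule censors patients at death, while the endpoint definition counts death as an event. The rule permits deaths to be left out of AASE without prescribing it. The 22-45% loss applies only under that reading, and it rests on assumed risks and on independence of death and non-fatal events; no rate in the article supports or refutes it.

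The conflicts between the text and Table 1 are a separate inconsistency. Both versions cannot be followed, although for binary data the choice of test changes little. Because the primary outcomes are feasibility measures and AASE is secondary in the trial, this is a clarification to make before unblinding. It does not undermine the design.

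**What to change.** 1. In Statistical analyses, state that death from any cause counts as an AASE event and that censoring for AASE applies only to withdrawal or loss to follow-up. Ending follow-up at death then applies only to outcomes of which death is not a component.
2. Define AASE per patient as any component event by 3 months. Report the proportion in each arm and the risk difference with a 95% confidence interval, and keep the patient-year rate as a descriptive figure only. State how withdrawn patients enter the denominator, since a plain proportion cannot carry censored time.
3. In the individual-events row of Table 1, replace the continuous type and t tests with the same binary method applied to adjudicated events. Repeat hospitalizations or emergency visits can still be counted descriptively.
4. List deaths among the individual events in the text as well as in Table 1.

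Kaplan-Meier estimates and competing-event methods are optional and not needed to resolve the point. The cost is a few sentences in one section and edits to two rows of Table 1, with no extra patients or visits.
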